### **9.2 Responsibilities of the Investigator(s)**

The Investigator(s) undertake(s) to perform the Clinical Trial in accordance with this Clinical Trial Protocol, ICH Guideline for Good Clinical Practice (GCP) Guideline (ICH E6R2 Step 4) approved on November 9, 2016) and applicable regulatory requirements in Hong Kong. These documents state that the informed consent of the subjects is an essential precondition for participation in the clinical study.

### **9.3 Subject Information**

An unconditional prerequisite for a patient participating in the study is his/her written informed consent. Adequate information must therefore be given to the subject by the Investigator(s) before informed consent is obtained. A person designated by the Investigator(s) may give the information, if permitted by local regulations. A subject information sheet in the local language and prepared in accordance with Good Clinical Practice will be provided by the Investigator(s) for the purpose of obtaining informed consent. In addition to this written information, the Investigator(s) or his/her/their designate will inform the subject verbally. In doing so, the wording used will be chosen so that the information can be fully and readily understood by laypersons.

The patient information sheet will be revised whenever important new information becomes available that may be relevant to the consent of patients.

### **9.4 Compensation to Subjects**

The patients do not receive payment for taking part in this trial. Patients who are entitled to discounted or free health care, e.g. civil servants, will receive their entitled free treatment as normal.

## **9.5 Ethics Committee or Institutional Review Board**

Prior to commencement of the study, the study protocol will be submitted together with its associated documents (patient information, informed consent forms,) to the institutional IRB for their favorable opinion. The favorable opinion/approval of the IRB will be filed in the study file. The study will only commence following provision of a written favorable opinion.

Any amendments to the protocol will be submitted to the IRB and they will be informed about SAEs in accordance with national and/or local requirements.

## **10. STUDY MANAGEMENT**

### **10.1 Data Quality Assurance**

The main objective is to obtain those data required by the study protocol in a complete, accurate, legible and timely fashion. The data in the Clinical Record Form (CRF) should be consistent with the relevant source documents.

The CRFs must be filled in completely and legibly (with either black or blue ballpoint pen, acceptable for use on official documents). Any amendments and corrections necessary must be undertaken and countersigned by the Investigator(s), stating the date of the amendment/correction. The Investigator(s) must state his/her reasons for the correction of important data. In the case of missing data/remarks, the entry spaces provided in the case report form should be cancelled out so as to avoid unnecessary follow-up inquiries.

The CRFs are regulatory documents and must be suitable for submission to authorities. According to the ICH guidelines for Good Clinical Practice, the Monitoring Team must check the CRF entries against source documents, except for the pre-identified source data directly recorded in the CRF. The Informed Consent Form will include a statement by which the patient allows the Sponsor's duly authorized personnel, the Institutional Review Board/Ethics Committee (IRB/EC), and the regulatory authorities to have direct access to source data which support the data on the CRF. Such personnel, bound by professional secrecy, must keep confidential all personal identity or personal medical information (according to confidentiality rules).

### **10.2 Direct Access to Source Data/Documents**

For the purpose of ensuring compliance with Clinical Trial Protocol, Good Clinical Practice and applicable regulatory requirements, the Investigator(s) should permit auditing by or on the behalf of the Sponsor and inspection by applicable regulatory authorities.

812 The Investigator(s) agree(s) to allow the auditors/inspectors to have direct access to the study  
813 records for review, being understood that this personnel is bound by professional secrecy, and  
814 as such will not disclose an personal identity or personal medical information.

815 The Investigator will make every effort to help with the performance of the audits and  
816 inspections, giving access to all necessary facilities, data, and documents.

817 As soon as the Investigator(s) is/are notified of a future inspection by the authorities, he will  
818 inform the Sponsor and authorize the Sponsor to participate in this inspection.

819 The confidentiality of the data verified and the protection of the patients should be respected  
820 during these inspections.

821 Any result and information arising from the inspections by the regulatory authorities will be  
822 immediately communicated by the Investigator(s) to the Sponsor.

823 The Investigator(s) shall take appropriate measures required by the Sponsor to take corrective  
824 actions for all problems found during the audit or inspections.

### 825 **10.3 Study File, Database and Archiving**

826 The Investigator(s) should have a study file for the study purpose. This file contains all  
827 relevant documents necessary for the conduct of the study. This file must be safely archived  
828 after termination of the study in accordance with the local relevant regulations.

829

## **APPENDIX 1. Prescription and Acceptance Criteria for SBRT (Modified from RTOG 1112 Protocol)**

### **(I) Target Volume Delineation**

The Gross Tumor Volume (GTV) is defined as all parenchymal and vascular HCC seen on MRI with gadoxetate disodium, and contrast-enhanced CT scan. Reference is also made with dual-tracer PET-CT scan images. GTV\_P1 should represent the ‘primary parenchymal (=P) dominant (=1)’ GTV, upon which primary quality assurance will be based. Subsequent lesions can be labeled as GTV\_P2, GTV\_P3,).

MRI, dual-tracer PET-CT and contrast-enhanced CT images must be co-registered with the planning CT for every subject recruited into this study (tumor-to-tumor registration is highly recommended).

The Clinical Target Volume (CTV): For each GTV\_P, the CTV is defined as the GTV (CTV\_P1... CTV\_P3), with no expansion. The minimal CTV\_P is the GTV\_P, with no expansion. It is expected that there will be no expansion from GTV to CTV for the majority of cases. Such CTVs may be treated to a microscopic dose (35 Gy) or up to as high as the prescription dose, at the investigator’s discretion. Separate CTVs should be labeled CTV\_P1, CTV\_P2, and CTV\_P3. The prescription dose should be annotated to each CTV after the final plan is complete (e.g. CTV\_P1\_50 for a 50Gy target, and CTV\_P2\_35 for a CTV treated to 35 Gy).

The Internal Target Volume (ITV): For each GTV\_P or CTV\_P, a margin may be added to account for the physiological motion of the tumors e.g. secondary to respiration or abdominal movements. The ITVs will be determined by the amplitude of the tumor and the liver based on 4D planning CT scans. For patients who will be treated with breath-hold technique, the ITV\_P is the GTV\_P with no expansion. Such ITV may be treated to a microscopic dose (35 Gy) or up to as high as the prescription dose, at the investigator’s discretion. Separate ITVs should be labeled ITV\_P1, ITV\_P2, and ITV\_P3. The prescription dose should be annotated to each ITV after the final plan is complete (e.g. ITV\_P1\_50 for a 50Gy target, and ITV\_P2\_35 for a ITV treated to 35 Gy).

The PTV will provide a margin around each ITVs to compensate for set-up. PTV nomenclature should follow GTV/CTV/ITV nomenclature guidelines. For example, PTV\_P for the PTV around the ITV\_P and PTV\_P1 and PTV\_P2 for PTVs around CTV\_P1 and CTV\_P2. A minimum PTV margin of 2–3 mm around each ITV is required in all directions. PTVs should not be manually modified due to proximity of adjacent OARs. The final PTVs should have dose annotated once the plan is final. Examples are PTV\_P1\_50 and PTV\_P1\_35 for targets treated to 50Gy and 35Gy, respectively.

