| Radiotherapy Planning | 
Radical radiotherapy will be delivered by stereotactic body radiation therapy (SBRT) which is described as follows:
 
SBRT will be delivered by either a 10MV linear accelerator (TrueBeam, Varian Medical System, US), Tomotherapy (Accuray) in the treating institution. Four-dimensional (4D) or breath-hold CT scanning for tracking the tumor and liver positions and radiation therapy planning is done with Real-time Patient Management (RPM) system (Varian Medical Systems, USA) or ExacTrac Adaptive Gating systems (Brainlab, AG, Germany) for motion detection. The gross tumor volume (GTV) with the co-registration of MRI and PET-CT images, and the motion of the
                                                                                                                                                                                                                                                                                                                                                                                                                                                                                                                                                                                                                                                                                                                                                                                                                                                    |

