## **4. STUDY TREATMENT**

### **4.1 Stereotactic Body Radiation Therapy (SBRT)**

Radical radiotherapy will be delivered by SBRT which is described as follows:

SBRT will be delivered by either a 10MV linear accelerator (TrueBeam, Varian Medical System, Palo Alto, USA) in the treating institution within 2 weeks of baseline investigations. Four-dimensional (4D) CT scanning for tracking the respiratory phases and radiation therapy planning is done with Real-time Patient Management (RPM) system (Varian Medical Systems, USA) or ExacTrac Adaptive Gating systems (Brainlab, AG, Germany) for motion detection. The gross tumor volume (GTV) with the co-registration of MRI and PET-CT images, and the motion of the tumor known as the internal target volume (ITV) are then contoured on the 4D CT images. The planning target volume (PTV) which encompasses the ITV with a 2–3mm margin, takes the set-up errors into account. Doses of SBRT range from 35Gy to 50Gy in 5 fractions over 5 to 14 days as adapted and modified from RTOG 1112 protocol, a phase 2 study investigating the use of sorafenib in combination with SBRT for inoperable HCC. The final dose is determined such that a maximum tumoricidal dose can be delivered to the tumors while the doses to the organs-at-risk are within the set tolerance

limits. Pretreatment positional verification by a cone-beam CT scanner, on-board imaging or other imaging devices available in each treating institution is done every time before SBRT with necessary correction if the linear and rotational displacement is more than 2mm and 2 degrees respectively. In addition, interval treatment verification with on-board x-ray imaging during SBRT may be performed additionally for identification of intra-fractional tumor displacement.

The details of target volume nomenclature and delineation as well as the acceptance criteria of SBRT are outlined in APPENDIX 1.

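### Appendix 1 lets the investigator choose 35 Gy for a breath-hold ITV defined as the GTV (and, on an ambiguous reading, for GTV-equal CTVs), against the highest-achievable-dose rule stated elsewhere

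*Protocol*

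**What the plan says.** **CTV.** Appendix 1, part (I) Target Volume Delineation, sets the CTV for each parenchymal lesion equal to its GTV, describes the GTV as the smallest the CTV can be, and adds: "It is expected that there will be no expansion from GTV to CTV for the majority of cases". The next sentence reads "Such CTVs may be treated to a microscopic dose (35 Gy) or up to as high as the prescription dose", with the choice left to the investigator. On labelling it says "The prescription dose should be annotated to each CTV after the final plan is complete", and its examples include a first-lesion CTV at 50 Gy and a second-lesion CTV at 35 Gy.

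**ITV.** With 4D planning the ITV allows for tumour motion. With breath-hold treatment the ITV is the GTV and nothing more. The sentence directly after that reads "Such ITV may be treated to a microscopic dose (35 Gy) or up to as high as the prescription dose", again at the investigator's choice. Breath-hold is an intended technique: the synopsis, under Radiotherapy Planning, has "Four-dimensional (4D) or breath-hold CT scanning for tracking the tumor and liver positions". Section 4.1 describes only 4D CT.

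**Dose rule elsewhere.** Section 4.1 says "The final dose is determined such that a maximum tumoricidal dose can be delivered to the tumors", subject to the organ tolerances. Appendix 1, part (III), makes the largest permitted dose to the primary target the goal. Part (IV) asks for the largest doses to target volumes that respect normal-tissue limits, steps the dose down through 50, 45, 40 and 35 Gy when the mean liver dose limit is exceeded, and sets full CTV coverage by the prescription dose as a goal. PTV Dosimetry asks for the highest dose compatible with the constraints and accepts less than the schedule where nearby GI luminal organs require it.

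**The concern.** The word microscopic normally describes a dose to tissue at risk around visible tumour. Here it is attached to a volume that, for breath-hold patients, is visible tumour by definition. A planner who follows part (I) literally may prescribe 35 Gy to gross HCC when the mean liver dose and the organ limits would permit 40, 45 or 50 Gy. A planner who follows section 4.1 or part (IV) may not. The protocol then holds two dose rules for the same target.

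This bears on delivery of the intervention. PTV Dosimetry justifies high doses by an observed dose response, and best objective response is listed among the primary endpoints in section 8.1.1. An instruction that permits a lower gross-tumour dose without an organ-limit reason works against that intent. It also leaves unclear whether such a plan is compliant.

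**Working it through.** **1. Which volume does the clause cover?**

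- *ITV sentence.* Its immediate antecedent is the breath-hold ITV, which the preceding sentence equates with the GTV. No other reading is offered for breath-hold patients. A 4D ITV also contains the GTV.
- *CTV sentence.* Its immediate antecedent is the unexpanded CTV. Yet the text calls the GTV the minimal CTV and speaks of a majority without expansion, which implies a minority with expansion. The clause can be read as referring to that minority, so this half is ambiguous rather than plainly wrong.

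**2. What else permits a lower dose to gross tumour?** Part (IV) names the mean liver dose, with limits of 13 Gy at 50 Gy, 15 Gy at 45 and 40 Gy, and 15.5 Gy at 35 Gy. PTV Dosimetry names GI luminal structures, and the compliance text for critical structures names non-hepatic organs. All are constraints. Outside part (I), nothing allows a reduction by investigator choice alone.

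**3. Size of the gap and how it is graded.** The inputs are the four prescription levels in part (III), the 35 Gy in part (I), and the PTV Dosimetry table for PTVs around GTVs. In that table, within 5% of prescription is per protocol, below 90% is an unacceptable deviation, and so is below 32 Gy.

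Gap = prescription − 35. Score = 35 / prescription.

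| Prescription used as reference | Gap | Score | Grade in the GTV column |
|---|---|---|---|
| 50 Gy | 15 Gy | 35/50 = 70.0% | unacceptable deviation |
| 45 Gy | 10 Gy | 35/45 = 77.8% | unacceptable deviation |
| 40 Gy | 5 Gy | 35/40 = 87.5% | unacceptable deviation |
| 35 Gy, annotated as the target's own prescription | 0 | 35/35 = 100% | per protocol, and above 32 Gy |

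**4. Which reference applies?** Both can be argued. Part (I) annotates a dose to each CTV and ITV after planning and says of PTVs "The final PTVs should have dose annotated once the plan is final", with examples "for targets treated to 50Gy and 35Gy, respectively". Part (IV) plans each PTV to one of the four levels, and PTV Dosimetry judges the coverage of each PTV separately. These rules support the last row. If the reference is instead the level that the mean liver dose schedule would allocate, one of the first three rows applies. The same plan is then either an unacceptable deviation or fully per protocol.

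**5. Does the rest of PTV Dosimetry settle it?** In part. Its text says that PTVs not treated according to the guidelines are an unacceptable deviation, and then asks for the highest dose within the constraints. A discretionary 35 Gy offends that text even when the percentage reads 100%. But the part (I) permission is itself one of the guidelines, so the conflict returns.

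**The case against.** The best defence is that the intent is clear. A microscopic dose makes sense only outside gross tumour. The PTV Dosimetry table has a separate column for PTVs around volumes that are not GTV, and the annotation examples show a 50 Gy and a 35 Gy PTV under one lesion label. The highest-dose rule is repeated in several places, and a radiation oncologist is unlikely to under-dose visible HCC on the strength of one permissive sentence. In addition, 35 Gy is itself an allowed level, and different lesions may receive different doses.

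Much of this stands. The clause was probably meant for volume beyond the GTV, and for the CTV that reading is available from the text. For the breath-hold ITV it is not, because the only volume described is the GTV. That 35 Gy is an allowed level does not help either: part (III) selects the level on normal-tissue constraints, not on preference.

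Three stronger readings are tempting, and the documents do not support them:

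- *Compliance review would miss such a plan.* Only the percentage row could pass it, and only if 35 Gy is annotated as that target's own prescription. The text around the table would still count against the plan.
- *The protocol intends gross tumour to receive 35 Gy by choice.* Section 4.1 and part (IV) say the opposite.
- *The response rate or sample size is compromised.* The sample size calculation does not use dose, dose already varies from 35 to 50 Gy by design, and nothing in the protocol quantifies a loss of response.

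**Conclusion.** The point holds as a contradiction in a treatment instruction. It is firm for the breath-hold ITV and ambiguous for the CTV. Read literally, part (I) allows gross tumour to receive 15, 10 or 5 Gy less than the constraints would permit at the 50, 45 and 40 Gy levels, with no organ-limit reason.

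The 15 Gy maximum is the full width of the allowed dose range. It is reached only if an investigator uses the clause where 50 Gy is achievable. How often that would happen, and what it would do to response, cannot be derived from the documents. The conclusion assumes that planners work from the wording of Appendix 1 and that breath-hold patients will be treated, as the synopsis and the appendix foresee. It should be corrected because the dose rule is wrong as written and the repair is cheap, not because harm to the trial's result has been shown.

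**What to change.** In Appendix 1, part (I):

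1. Reword the CTV sentence so that the discretionary 35 Gy applies only to any part of a CTV extending beyond the GTV.
2. Reword the ITV sentence so that it applies only to any part of an ITV extending beyond the GTV and its motion.
3. Add one sentence: volumes covering the GTV, including the breath-hold ITV, follow parts (III) and (IV), that is, the highest of 50, 45, 40 or 35 Gy that the mean liver dose and organ-at-risk limits allow, with priority to the primary target when several lesions share the mean liver dose limit.

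The cost is two reworded sentences and one new one, submitted to the IRB as an amendment under section 9.5. Sample size, visits and data collection do not change.

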### **(II) Critical Structures or Organs-at-Risk Delineation**

The following critical normal structures (known as organs-at-risks [OAR] must be contoured by the investigator(s) for each patient:

875  
876 Liver  
877 Liver minus GTVs  
878 Esophagus  
879 Stomach  
880 Duodenum  
881 Small bowel  
882 Large bowel  
883 Gallbladder  
884 Common bile duct  
885 Spinal cord  
886 Spinal cord PRV5 (spinal cord + 5mm)  
887 Right kidney  
888 Left kidney  
889 Skin  
890 External chest wall  
891 Heart  
892 Ascites (if present, for treatment positional verification only though no constraint will be applied  
893 to treatment plan optimisation)  
894 Subphrenic fat (if present, for treatment positional verification only though no constraint will be  
895 applied to treatment plan optimization)  
896

### 897 (III) Prescription Dose

898 Absorbed dose: 35Gy to 50Gy in 5 fractions. The prescription dose may be 50Gy, 45Gy, 40Gy,  
899 or 35 Gy in 5 fractions, based on normal tissue constraints. The dose to multiple PTVs may be  
900 different. The goal is to use the highest allowable prescription dose to the primary target, while  
901 respecting normal tissue constraints. The minimal planned prescription dose to PTVs is 35Gy.  
902

### 903 (IV) Dose Specifications

904 The prescription isodose should encompass 95% of PTV. The dose to multiple PTVs within the  
905 same patient may vary. If there are multiple PTVs, each should be planned for one of the  
906 prescription doses listed above, with each specific covering isodose planned to encompass 95%  
907 of each PTV, with normalization to the PTV receiving the highest dose. The highest allowable  
908 doses to the target volumes that maintain normal tissue constraints should be used. A goal is that  
909 100% of the CTV is encompassed by the prescription dose. The unit of dose is Gy.  
910

911 Dose prescription is based on the volume of normal tissues irradiated (correlated with mean liver  
912 dose), as well as proximity of stomach, duodenum, small and large bowel (GI luminal structures)  
913 to the target volumes, as normal tissue constraints must be maintained in this study.  
914

915 In the absence of adjacent GI luminal structures that may limit dose, the PTV dose prescription  
916 should be as high as possible based on mean liver dose (MLD, defined as the mean dose to the  
917 liver minus all GTVs), with 4 potential dose levels: Use of effective liver volume (Veff) to aid in  
918 dose allocation is permitted but not mandatory. If there are discrepancies in the Veff and MLD  
919 for the prescription dose allocation, MLD has priority.

| Priority Constraint                       | Optional Constraint | Prescription Dose    |                                                             |
|-------------------------------------------|---------------------|----------------------|-------------------------------------------------------------|
| Mean liver dose
(liver minus all GTVs) | Liver Veff          | Planned prescription | If the maximum allowed MLD is exceeded at this planned dose |
| 13                                        | < 25%               | 50                   | Reduce to 45 Gy and re-evaluate                             |
| 15                                        | 25-29%              | 45                   | Reduce to 40 Gy and re-evaluate                             |
| 15                                        | 30-34%              | 40                   | Reduce to 35 Gy and re-evaluate                             |
| 15.5                                      | 35-44%              | 35                   | Do not treat; out of study                                  |

